**Routine clinical outcomes on clients with personality difficulties (measured in 6 m before and after the workshop)**		
** Depression symptoms**	Patient Health Questionnaire (PHQ-9 [44];)—a 9-item self-report measure of frequency of depression symptoms (for example, ‘Little interest or pleasure in doing things’). Respondents are asked to rate frequency of symptoms over the past 2 weeks on a 4-point Likert scale from ‘Not at all’ to ‘Nearly every day’. This scale is validated for use in adolescents and adults.	First and last session
** Anxiety symptoms**	The Generalised Anxiety Disorder scale (GAD-7; [45])—a 7-item measure of anxiety symptom (for example, ‘Feeling nervous, anxious or on edge’) frequency over the past 2 weeks, scored on a 4-point Likert scale from ‘Not at all’ to ‘Nearly every day’.	First and last session
** Work and social functioning**	Work and Social Adjustment Scale (WSAS; [46])—a 5-item measure of impairment in daily functioning (for example, ‘Because of my [problem] me ability to work is impaired’) rated on a 9-point Likert scale from ‘Not at all’ to ‘Very severely’.	First and last session
** Measure of personality difficulties**	Standardised Assessment of Personality: Abbreviated Scale—Self Report version (SAPAS-SR; [47, 48])—8-item binary response (yes/no) measure of personality difficulties (for example, ‘In general, do you have difficulty making and keeping friends. This scale is adapted for use as a self-report questionnaire and respondents are asked to indicate ‘Yes’ when the experience applies to them ‘most of the time in most situations’. This scale has been widely used for rapid screening for personality difficulties within the TTad setting for research purposes and has been adopted into routine practice in some services [4, 5, 9].	First session /instance
** Qualitative experiences of treatment**	Patient Experience Questionnaires	Treatment end

**Table 2 Tab2:** Feasibility and acceptability data, method of measurement, and continuation rule to proceed to randomised evaluation without modification

Feasibility/acceptability outcome	Measurement	Continuation rule
**Recruitment**	*Quantitative data*	
	Number of TTad sites recruited to the research project	≥ 3 IAPT sites recruited
	Percentage of eligible therapists attending the training at each site	≥ 60% attendance
	Percentage of attending therapists completing pre- and post-training surveys	≥ 80% data availability

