	Percentage of attending therapists completing 3-month follow-up surveys	≥ 60% data availability
**Acceptability**	*Quantitative data*	
	Feedback data on training (that that the training was theoretically interesting, clinically useful, well presented, and would recommend to other HICBT therapists)	60% agree or strongly agree with each item
	*Qualitative data*	
	Written feedback from therapists on the value of training	No significant concerns emerge about training that cannot be resolved
	Qualitative interviews with therapists	No significant concerns emerge about training that cannot be resolved
	Reporting/identification of serious concerns about the acceptability and feasibility of training by key stakeholders	No serious concerns emerge about training that cannot be resolved
	Reporting/identification of serious negative consequences for therapist participants or the clients they subsequently work with as a result of the training (unexpected, clearly research- or training intervention-related serious adverse reactions).	No serious consequences raised
**Clinical outcome data completion**	*Quantitative data*	
	Percentage of TTad clients receiving routine care during the study with sufficient data for inclusion in secondary analyses (at least one measure of SAPAS-SR personality difficulties and at least × 2 measures of the TTad service minimum dataset [PHQ-9, GAD-7 and WSAS])	≥ 60% data availability
**Proof-of-concept**	*Quantitative data*	
	Therapist attitudinal change in confidence to recognise, assess and triage clients with personality difficulties; to adapt key skills for working therapeutically with this group; and in positivity towards working with this group after completing the training in each service.	Significant improvement from pre to post in all 5 attitudinal domains

In addition to these measures, we will capture clinical data to enable us to generate metrics of engagement including discharge code and number of sessions marked ‘Attended’, ‘Did Not Attend’, and ‘Patient Cancelled’. In line with standard reporting of TTad outcomes, we will also compute the following metrics from clinical outcomes: (i) ‘Recovery’—as defined by moving ≥ 10 to ≤ 9 on the PHQ-9 and from ≥ 8 to ≤ 7 on the GAD-7; (ii) ‘Reliable Improvement’—as defined by improving by ≥ 6 points on the PHQ-9 or ≥ 4 points on the GAD-7; and (iii) ‘Reliable Recovery’—as defined by fulfilling criteria for both ‘recovery’ and ‘reliable improvement’ [49].

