#### Clinical outcomes

We will report descriptive statistics (means, standard deviations) to describe the clinical measures and client characteristics at intake within the pre- and post-training intervention cohorts (those engaging in treatment in the 6 months pre- compared to 6 months post-therapist training). This will include PHQ-9, GAD-7, and WSAS mean scores; the proportion of clients showing mild, moderate, and severe cut-offs on each scale; and the proportion of clients scoring 3 or more on the SAPAS-SR (indicative of personality difficulties).

This research is a multi-site observational study prior to conducting a definitive evaluation with a randomised trial and therefore has not been a priori powered to inferentially examine between cohort differences in clinical outcomes. However, it is both possible and useful to estimate the between-cohort effect size (and their 95% confidence interval) on client outcomes to help inform decisions to continue to a definitive evaluation of the training intervention and to inform future power calculations. We will therefore report the observed effect sizes but not *p* values. These analyses will focus solely on the subgroup of participants meeting the criteria for probable personality disorder (3 or more on the SAPAS-SR), which we estimate from previous research to be between 69 and 81% of client treatments [5, 9]. A series of linear regressions will examine whether treatment-cohort (treated before or after training) predicts the number of treatment sessions attended and post-treatment levels of depression (PHQ-9), anxiety (GAD-7), and functioning (WSAS). All analyses will include the training site as a covariate. The post-treatment analyses will adjust for the pre-treatment level of the relevant variable. Comparable binary logistic regressions will examine binary outcomes (rates of reliable improvement, recovery, and reliable recovery; rates of clients with planned discharges), again seeing if the treatment cohort (before or after training) predicts each variable and covarying for the training site. As we do not anticipate sufficient statistical power to do inferential statistics, we will examine the distribution of effect sizes, potentially using confidence intervals and Bayesian methods relative to estimates of minimum clinically important difference on clinical outcomes (cf., [55–58]). All quantitative analyses will take place in SPSS or R.

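### As written, Reliable Improvement counts a client as improved even if the other symptom scale worsens by the plan's own threshold; the effect is small and the correction is cheap

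*Protocol article*

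**What the plan says.** The text below Table 2 of the protocol article introduces three derived client metrics: "In line with standard reporting of TTad outcomes, we will also compute the following metrics from clinical outcomes". It cites a reference for them.

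- Recovery is defined "as defined by moving ≥ 10 to ≤ 9 on the PHQ-9 and from ≥ 8 to ≤ 7 on the GAD-7", so both scales must cross their cut-offs.
- Reliable Improvement is defined "as defined by improving by ≥ 6 points on the PHQ-9 or ≥ 4 points on the GAD-7". One scale is enough, and nothing is asked of the other.
- Reliable Recovery is defined "as defined by fulfilling criteria for both ‘recovery’ and ‘reliable improvement".

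No other section adds a no-worsening condition or defines a category of reliable deterioration. Under Statistical methods, Clinical outcomes, the metrics become regression outcomes: "Comparable binary logistic regressions will examine binary outcomes (rates of reliable improvement, recovery, and reliable recovery; rates of clients with planned discharges". The predictor is cohort (treated before or after the training), with site as covariate. The analysis is exploratory: "We will therefore report the observed effect sizes but not *p* values". The same section, and the section on the service-level secondary data sample, say that the client results will inform the power calculation for the randomised evaluation.

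**The concern.** A fall of 6 PHQ-9 points or 4 GAD-7 points is taken as large enough to be reliable. A rise of the same size is then reliable too, yet the rule ignores it whenever the other scale has improved enough. A client with GAD-7 down 4 and PHQ-9 up 10 is labelled improved.

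Two things are at stake. The first is the absolute rate of reliable improvement, which is reported and carried into planning; a mixed outcome counted as an improvement can only raise it. The second is the comparison between cohorts, if the share of mixed outcomes changes after the training.

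**Working it through.** The article gives no rate, SD or correlation for this metric, so there is no figure of its own to reproduce. The check has three parts.

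**1. What the rule admits.** Write P for the fall in PHQ-9 and G for the fall in GAD-7 (negative means worse).

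- Rule as written: P ≥ 6 or G ≥ 4.
- Guarded rule: (P ≥ 6 or G ≥ 4), and neither P ≤ −6 nor G ≤ −4.

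PHQ-9 12 to 6 gives P = 6. GAD-7 8 to 18 gives G = −10, and 10 / 4 = 2.5 thresholds of worsening. The rule as written is met; the guarded rule is not. The same split occurs for PHQ-9 20 to 14 with GAD-7 10 to 21 (P = 6, G = −11).

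**2. Which metrics are touched.** Recovery needs the PHQ-9 to go from at least 10 to at most 9 and the GAD-7 from at least 8 to at most 7, so P ≥ 1 and G ≥ 1. Neither scale can have worsened. Reliable Recovery requires Recovery, so it cannot contain a mixed outcome either. Listing every first and last score pair confirms this, taking ranges of 0–27 and 0–21 (items scored 0–3, an assumption): none of the 20,160 combinations that meet Recovery has reliable worsening. Of the 213,253 combinations that meet Reliable Improvement, 86,526 do. That is a count of possible score patterns, not a frequency among clients.

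**3. How often, and with what effect.** Assumptions, none from the article: change scores bivariate normal and rounded, SDs 6.5 (PHQ-9) and 5.5 (GAD-7), 2 million draws. The excess is the rate as written minus the guarded rate.

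| Mean fall (PHQ-9, GAD-7) | Correlation | As written | Guarded | Excess (points) | Share of those labelled improved |
|---|---|---|---|---|---|
| 5.5, 4.5 | 0.4 | 72.2% | 69.6% | 2.6 | 3.6% |
| 5.5, 4.5 | 0.6 | 68.6% | 67.5% | 1.0 | 1.5% |
| 5.5, 4.5 | 0.75 | 65.4% | 65.1% | 0.3 | 0.4% |
| 3, 2.5 | 0.4 | 56.8% | 53.3% | 3.5 | 6.1% |
| 3, 2.5 | 0.6 | 53.4% | 52.0% | 1.4 | 2.6% |
| 3, 2.5 | 0.75 | 50.3% | 50.0% | 0.3 | 0.7% |

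Excess and share were computed before rounding. With SDs of 6 and 5.3, mean falls of 5/4.5 or 3/3 and correlations of 0.4 to 0.8, the excess is 0.1 to 2.7 points, so the order of magnitude is stable.

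In numbers of clients: the article expects about 2,400 per cohort, 69 to 81% of them in the analysed subgroup, that is 1,656 to 1,944. Then 0.003 × 1,656 ≈ 5 and 0.035 × 1,944 ≈ 68 clients per cohort, before missing data.

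**Cohort contrast, both scales 0.2 SD better after training.** The largest gap is at correlation 0.4 with mean falls 3 and 2.5: odds ratio about 1.44 as written and 1.45 guarded. At correlation 0.75 the two agree to within about 0.002. The written rule gives the slightly smaller effect.

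**Cohort contrast, scales moved 0.2 SD in opposite directions.** The written rule is more favourable to the training by 0.2 to 1.1 percentage points. If the GAD-7 is the scale that improves, the guarded rule still shows a gain of about 1.3 to 3.1 points. If the PHQ-9 improves, the written rule shows about no change and the guarded rule a loss of 0.3 to 1.1 points.

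**The case against.** The strongest reply is that little depends on this. The metric is exploratory and reported without p values. No continuation rule in Table 2 uses it; the proof-of-concept rule there concerns therapist attitudes. Post-treatment PHQ-9 and GAD-7 are each regressed separately on cohort, so opposing shifts in the means would show. All of this stands and sets the grade of the point. The separate regressions do not, however, show how many individual clients improved on one scale and worsened on the other, nor do they correct the labelled rate.

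A second reply is that the article says it follows standard service reporting and cites a source, and that a full study protocol exists. Neither is shown, so either may contain the missing condition. That cannot be settled here. But the article does not leave the rule open: it states explicit thresholds joined by 'or', and anyone coding from it would count these clients as improved.

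A reader might infer more: that each mixed outcome tilts the evaluation towards the training, or that the rule would conceal harm. The documents do not support that. Both cohorts are scored by the same rule, and when both scales improve the written rule slightly understates the effect. A reader might also expect frequent mixed outcomes because the workshop description speaks of clients with unstable presentations. That remark concerns how sessions are structured, and says nothing about the two scales moving apart.

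**Conclusion.** The point holds in a limited form. The stated rule labels as reliably improved a client who has worsened on the other scale by the plan's own threshold. The consequence is a small upward bias in one absolute rate, about 0.3 to 3.5 points under the assumed SDs, means and correlations; the low end applies if the scales change closely together. The rate matters because the client results feed the planning of the next trial. The between-cohort contrast is practically unchanged, except for a favourable bias of about 0.2 to 1.1 points when the scales move in opposite directions by 0.2 SD. Reading this as an overstatement of the training's effect in general, or as a threat to the decision to continue, goes beyond what the article supports. It is a minor correction.

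**What to change.** Define Reliable Improvement as improvement of at least 6 on the PHQ-9 or at least 4 on the GAD-7, with no worsening of at least 6 on the PHQ-9 or at least 4 on the GAD-7. Apply it to both cohorts and recompute every rate and regression of this outcome. If the cited source already contains such a condition, say so in the definition. The cost is one clause, one line of code and a slightly lower reported rate. Recovery needs no change, and Reliable Recovery keeps the same members.

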### Participant timeline

Pre-training surveys will be distributed 2 weeks before the training workshop. Post-training surveys will be distributed at the end of the workshop and follow-up surveys 3 months after the training. All HICBT therapists employed at participating sites will have the opportunity to attend the training, regardless of their intention to participate in the research. All training attendees will be invited to take part in the research.

### Qualitative interviews

Approximately 1 month after the training, a subsample of therapists who took part in the training and consented to take part in the research will be invited to take part in a remote (telephone or videoconferencing) qualitative interview to explore their experiences (including any challenges) of treating individuals with personality difficulties in TTad services, their perceptions of the workshop, and whether the workshop has led to any changes in their practice or their workplace wellbeing. We will purposefully sample participants who vary in relation to (i) study site, (ii) quantitative and qualitative written feedback on the workshop, (iii) attitudinal change (pre-post), and (iv) therapist experience level.

The therapist sampled will be contacted by email, provided with a 'Participant Information Sheet’ and given an opportunity to discuss participating with a member of the research team. To ensure consistency across the interviews, a topic guide will be used (Additional file 5: Appendix 5). It will be based on the aims of the research and team discussions and informed by the COM-B model of behaviour change and Normalisation Process Theory [29, 50]. With participant consent, all interviews will be audio-recorded and transcribed verbatim. They will be analysed thematically, using the framework analysis approach [51] to help make comparisons within and across the interviews.

### Sample size

#### Therapists

The final therapist sample size will be determined by the number of therapists participating in the training at each of the three participating sites. Based on our previous experience, we anticipate that approximately 40 therapists will attend at each site (120 total). Based on similar studies examining the effects of training for healthcare professionals on attitudes and behaviours (e.g. [52, 53]), we anticipate the effect size of training on change in therapist attitudes and perceived self-efficacy to work with this client group to be at least *d* = 0.4. A G*Power [54] calculation indicates that the required sample size to detect a medium effect of *d* = 0.4 in a paired samples two-tailed *t* test, with 80% power is *n* = 84. Assuming 120 therapists attend the training, with 80% data completion, we will have 96 participants to analyse. This is sufficient power to detect a small-medium (*d* ≥ 0.27) pre-post effect size on these therapist ratings.

A sub-sample of therapist participants will be invited to take part in an in-depth qualitative interview about their experiences of the training. We anticipate undertaking up to 20 interviews, guided by ‘data saturation/information power’ relevant to the study objectives.

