#### Therapist outcomes

We will report descriptive statistics (means, standard deviations) to describe the attitudes of therapists before and after the training intervention on each individual rating.

Considering pre to post as our primary outcome for therapist attitudinal change, we will use a series of paired samples two-tailed *t* tests (or an equivalent non-parametric test if that data is not adequately normally distributed) and report effect size (Cohen’s D) to establish preliminary proof of concept that training is significantly associated with positive change in therapist reported confidence to recognise, assess, and triage clients with personality difficulties; formulate clients with these difficulties; anticipate challenges to alliance; and adapt key skills for working therapeutically with these clients, in addition to positive change in attitudes towards working with this group. As a secondary exploratory analysis, we will perform repeated measures ANOVAs including all three timepoints (pre-, post-, and 3-month follow-up).

If we recruit a sufficient sample size (at least 120 × therapists across the 3 sites, with 80% data completion, and therefore 96 complete cases to analyse), we will also use exploratory moderation analyses to explore whether the site, therapist experience (number of years post-qualification), ethnicity (white British vs. other), gender (male/female/non-binary), and experience level moderate the extent of change in attitudes observed during the training.

We will also address whether training has an impact on the rapist-reported wellbeing (SWEMWBS) or workplace burnout (SBI). We will report descriptive statistics to describe the wellbeing and burnout of therapists before and after the training intervention and use paired sample two-tailed tests (or a non-parametric equivalent if data is not adequately normally distributed) to establish if there is significant change in these secondary outcome measures.

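### The therapist power figures are wrong: 84 pairs give 95% power at d = 0.4, not 80%, and 96 completers fall short of 80% power at d = 0.27

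*Protocol article*

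**What the plan says.** The section Sample size, Therapists, in the protocol article makes two linked power statements.

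- **Required number.** The effect of training on therapist attitudes is expected "to be at least *d* = 0.4". For an effect of that size the article reports a G*Power result, worded as follows: "paired samples two-tailed *t* test, with 80% power is *n* = 84".
- **Sensitivity of the expected sample.** The article expects that "approximately 40 therapists will attend at each site (120 total"), and "with 80% data completion, we will have 96 participants to analyse". It concludes: "This is sufficient power to detect a small-medium (*d* ≥ 0.27) pre-post effect size on these therapist ratings".

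The section Therapist outcomes names the same test for the pre-to-post attitude ratings: "we will use a series of paired samples two-tailed *t* tests", with a non-parametric alternative if the data are not adequately normal. No significance level is stated.

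**The concern.** A required sample of 84 is too large for a paired test of d = 0.4 at 80% power, and 0.27 is too small an effect for 96 pairs to detect at that power. The two errors run in opposite directions, so one slip in one input cannot explain both.

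These are the only power figures in the article, and its description of the intervention characterises the planned therapist evaluation as adequately powered. The same t tests feed the proof-of-concept continuation rule in Table 2, which requires significant improvement in all five attitudinal domains. Anyone interpreting a non-significant item needs the true sensitivity of the sample. Attendance fixes the final number of therapists, so a reader faced with 52 to 83 completers would also take the study to have missed its stated requirement when it had not.

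**Working it through.** **Inputs**

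| Input | Value | Source |
|---|---|---|
| Test | paired t test, two-tailed | Sample size, Therapists; Therapist outcomes |
| Power | 80% | Sample size, Therapists |
| Anticipated effect | d = 0.4 | Sample size, Therapists |
| Stated required n | 84 pairs | Sample size, Therapists |
| Expected completers | 120 × 0.80 = 96 | Sample size, Therapists |
| Stated detectable effect with 96 | d = 0.27 | Sample size, Therapists |
| Alpha | 0.05 two-sided | assumption; not stated |

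**Formula.** For n pairs, d is the mean change divided by the SD of the change. The test statistic follows a non-central t distribution with n − 1 degrees of freedom and non-centrality d√n. Power is the probability that its absolute value exceeds the two-sided critical value of t.

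**Step 1. Trying to reproduce n = 84.** The smallest n at d = 0.4 is:

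| Power | n |
|---|---|
| 80% | 52 |
| 90% | 68 |
| 95% | 84 |

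- n = 52: non-centrality 0.4 × √52 = 2.884, critical value 2.008, power 80.8%.
- n = 84: non-centrality 0.4 × √84 = 3.666, critical value 1.989, power 95.2%. With n = 83, power is 94.96%, so 84 is exactly the first n to reach 95%.
- The normal approximation, ((1.960 + 0.842)/0.4)² = 49.1, rounds up to 50 and agrees closely with 52.

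The stated requirement exceeds the correct one by (84 − 52)/52 = 62%.

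**Step 2. Trying to reproduce d = 0.27 with 96 pairs.** Non-centrality is 0.27 × √96 = 2.645 and the critical value is 1.985, so power is 74.5%. The effect detectable with 80% power is d = 0.289. Reaching 80% power at d = 0.27 takes 110 pairs. If the intended power was the 95% that 84 implies, 96 pairs detect only d = 0.372, which is further from 0.27.

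**Step 3. Does another choice of inputs explain the figures?** Required n at d = 0.4 and 80% power:

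| Variant | n |
|---|---|
| One-sided alpha 0.05 | 41 |
| Two-sided alpha 0.025 | 62 |
| Two-sided alpha 0.01 (0.05 over five items) | 77 |
| Two-sided alpha 0.005 | 88 |
| 52 inflated for 80% completion (52/0.80) | 65 |
| Wilcoxon, worst-case efficiency 0.864 (52/0.864) | 61 |
| Two-sample test | 99 per arm |

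None gives 84. A one-sided test would support d = 0.27 (83.7% power with 96), but both sections specify two-tailed tests. Reading d as change over the raw SD does not help either: 84 would need a pre-post correlation of 0.16, and 0.27 would need 0.56.

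**Step 4. Consistency without assuming alpha.** At fixed alpha and power, the detectable effect scales approximately with 1/√n. If 84 pairs gave 80% power at d = 0.4, then 96 pairs would detect about 0.4 × √(84/96) = 0.374, not 0.27. Solving for alpha directly, 84 pairs need a two-sided alpha of about 0.006, while 0.27 with 96 pairs needs about 0.075.

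**The case against.** The strongest reply concerns consequence. The first error is conservative: 96 exceeds both 52 and 84, and gives 97.3% power at d = 0.4. Nothing in the plan uses 84 as a threshold. Attendance sets the sample, the data-completeness rules in Table 2 are percentages, and the only numeric condition on an analysis, 96 complete cases for the moderation analyses, comes from 120 × 0.80. The second error is about 0.02 SD and lies below the anticipated effect. The primary analyses of this feasibility study are descriptive. All of this stands: the sample, the analyses and the decision rules need no change.

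Two further points stand in part.

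- The sentence on d = 0.27 speaks only of sufficient power. However, 80% is the only level in the paragraph, and the 95% reading makes the claim worse.
- Alpha is not stated, so 52 and the 62% excess hold for 0.05. At 0.01 the requirement would be 77. The size of the first error therefore depends on alpha, but the conflict between the two sentences does not.

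**Conclusion.** The concern holds. As written, both figures are wrong, and they cannot both be true at any one significance level. At two-sided alpha 0.05, with d defined on the SD of the change:

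- the requirement for 80% power at d = 0.4 is 52, not 84;
- the effect detectable with 96 completers at 80% power is 0.289, not 0.27, and power at 0.27 is 74.5%.

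The exact match of 84 to 95% power suggests a mislabelled power level, although the article does not show the cause. This is an error in the stated justification. It does not mean that the planned sample is too small for d = 0.4 on a single item.

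**What to change.** Replace the two sentences with wording such as:

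> For a two-sided paired t test at alpha 0.05 on a single attitude item, with sites pooled and d defined as the mean change divided by the SD of the change, 52 completers give 80% power at d = 0.4 (84 give 95%). The expected 96 completers give 97% power at d = 0.4, and 80% power for d of 0.29 or more.

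The limit to a single item with sites pooled should stay in the text. The proof-of-concept row of Table 2 asks for significance in all five domains and refers to change in each service. If that means a test per service, about 32 completers per site (96/3) give roughly 59% power per item at d = 0.4, so the 97% must not be read as the chance of meeting that rule.

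The cost is a text correction. One stated figure becomes slightly less favourable (0.27 becomes 0.29), and recruitment and analyses are unaffected.
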